### 2.4. Vibration Platform

A horizontal oscillating platform (Galileo 2000©, CELDUAL, S.L., Valencia, Spain) with an amplitude of 2 mm and a constant frequency of 14 Hz will be used as a WBV instrument.

### 2.5. Procedure

Participants with type 2 diabetes will be recruited through talks, on alternate days, at the diabetic association of Plasencia (Cáceres). Those who wish to participate and meet the inclusion criteria will be contacted through a preliminary interview where they will be informed of the methodology, objectives, and process of the study and will be given an informed consent form that must be signed for their inclusion in the study. 

The screening will be performed by two physiotherapists and a research nurse at the University Center of Plasencia. The selected participants will undergo an interview where they will be asked about mobility disability and/or comorbidities incompatible with physical exercise in order to exclude those participants who do not meet the inclusion/exclusion criteria.

The study will be conducted from February 2024 to May 2024 by the aforementioned professionals. Participants will be randomly assigned to the intervention or control group, using a randomization list generated by a computer program. All participants who meet the above criteria will be offered entry into the study and will be given information and the schedule of interventions to participate in the study. Patients will continue with their usual lifestyle. After providing information about the study, they will be randomly included in one of the two groups (intervention or control).

Two of the researchers will be responsible for the correct control of the frequency and amplitude of the vibration platform during the entire intervention and for the correct performance of the exercises proposed for each training session, in addition to the functional tests TUG, 10MWT, and 5STS. A third researcher will be responsible for the determinations and parameters to be measured in the sample subjects (HbA1c and plasma glucose, lipid profile, weight, height, and blood pressure).

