### 2.1. Study Design and Setup

The study is a double-blind, randomized controlled trial with parallel group design in a 1:1 ratio.

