### 2.2. Participants

The study will be carried out with diabetic patients from the Plasencia area. Participants who wish to participate in the present study must meet the following inclusion criteria: healthy type 2 diabetic patients between the ages of 50 and 60 years who are not taking medication for diabetes. Exclusion criteria will be established as having some underlying pathology (such as diabetic retinopathy or diabetic nephropathy), mobility disability and/or comorbidities incompatible with physical exercise and the use of vibration platforms, previous hip or knee surgeries, cognitive impairment, and neurological pathology.

Given the lack of studies that allow us to calculate the sample size for the sample to be representative, a pilot study will be carried out to obtain these data. A total of 40 subjects (20 men and 20 women) will be evaluated, divided into a control group (n = 20) and an experimental group (n = 20) (Figure 1).

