### 2.6. Study Schedule

During the first week of February, detailed information on the procedure, informed consent, and the schedule of the study interventions will be provided. 

During the second week of February, preintervention measurements of HbA1c, lipid profile, blood pressure, height and weight, and TUG, 10MWT, and 5STS will be carried out so that they can be compared with the postintervention measurements.

During the following 12 weeks, the experimental group will carry out the intervention by means of the exercises in the WBV. These exercises will be performed three days a week, with a rest of at least 24 h between days of intervention.

In the third week of May, after the end of the intervention, the participants will again undergo HbA1c, lipid profile, weight, height, and TUG, 10MWT, and 5STS tests. The control group will also have their blood pressure measured (Figure 2).

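### As written, randomisation appears to come before the baseline tests; the protocol should put baseline first and carry its sex quota into the list

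*Protocol article*

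**What the plan says.** All references are to the protocol article.

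- **Design.** Section 2.1 describes a "double-blind, randomized controlled trial with parallel group design in a 1:1 ratio". It does not say who is blinded.
- **Allocation.** Section 2.5 assigns participants "using a randomization list generated by a computer program" and places this step as follows: "After providing information about the study, they will be randomly included in one of the two groups (intervention or control". No other event is used to time it.
- **Calendar.** Section 2.6 begins: "During the first week of February, detailed information on the procedure, informed consent, and the schedule of the study interventions will be provided". It continues: "During the second week of February, preintervention measurements of HbA1c, lipid profile, blood pressure, height and weight", with the three functional tests in the same week. Randomisation has no date of its own.
- **Baseline by arm.** Section 2.5.1 lists the baseline tests as something control participants undergo before they go back to their usual routine. Section 2.5.2 lists the same tests for intervention participants at the start of the intervention.
- **Who measures.** Under Section 2.5, the two researchers who control the platform sessions also conduct TUG, 10MWT and 5STS. A third researcher takes HbA1c, glucose, lipids, weight, height and blood pressure.
- **Numbers.** Section 2.2 states "A total of 40 subjects (20 men and 20 women) will be evaluated". Each arm is to have 20 of these participants, and no sex split within arms is given.
- **Analysis.** Section 2.7 plans a check of baseline similarity, a comparison at 12 weeks, a comparison of changes from baseline, and linear regression for confounders that it does not name.

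**The concern.** A team that follows the text in order would inform and consent participants, allocate them, and take baseline measurements a week later. By then participants would know their arm, because controls receive no sham. The people timing the functional tests would know it too, because they run the sessions.

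Sections on the 10MWT and 5STS ask for maximal speed, so the results depend on effort and encouragement. A baseline that differs by arm for this reason feeds directly into the change from baseline and into the baseline similarity check. A participant who withdraws after learning the arm but before being measured leaves no value to analyse, and the loss may be related to the arm.

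A smaller matter concerns sex. The protocol fixes the numbers of men and women, which makes sex a design factor, but nothing shown carries that factor into the allocation.

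**Working it through.** **1. Order of events.** Four places bear on it.

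| Place | What it implies about allocation |
|---|---|
| Section 2.5 | Follows the giving of information |
| Section 2.6 | Information in week 1, baseline in week 2; randomisation not dated |
| Section 2.5.1 | Baseline done on people already called control participants |
| Section 2.5.2 | Baseline done on people already called intervention participants |

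Allocation before baseline is the natural reading of these four, and nothing shown contradicts it. It remains an inference: an event that comes after information could also come after the week-2 baseline. Figures 1 and 2, which might settle it, are not available.

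**2. Effect on the analysis if allocation comes first.** Suppose knowledge of the arm makes mean baseline performance differ between arms by an amount d, with the 12-week values unaffected.

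- Comparison of 12-week values alone: shifted by 0.
- Comparison of changes: shifted by the full d, with opposite sign.
- Regression adjusted for baseline with slope b: shifted by b × d, with opposite sign.

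The documents give no basis for the size or direction of d. The exposure differs by outcome:

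- TUG, 10MWT, 5STS: participant and tester would both know the arm, and performance depends on effort.
- HbA1c and lipids: read by device and taken by the third researcher, so much less exposed.
- Blood pressure: also taken by the third researcher, but read from an aneroid gauge, so somewhere in between. Whether that researcher knows the arm is not stated.

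**3. Loss before baseline.** One participant lost from an arm of 20 is 1/20 = 5% of that arm. The number of such losses cannot be estimated from the documents.

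**4. Sex balance.** The plan gives no calculation to reproduce here. Its totals agree: 20 men + 20 women = 40, and 20 + 20 per arm = 40. Assume a list forced to 20 per arm and *not* stratified by sex. The number of men k in one arm is then hypergeometric:

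P(k) = C(20, k) × C(20, 20 − k) / C(40, 20)

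| Split of men between arms | Probability |
|---|---|
| exactly 10/10 | 0.248 |
| 12/8 or worse | 0.343 |
| 13/7 or worse | 0.113 |
| 14/6 or worse | 0.026 |

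The SD of k is √(20 × 0.5 × 0.5 × 20/39) = 1.60.

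With a simple unrestricted list, arms of exactly 20 and 20 would arise with probability C(40, 20)/2⁴⁰ = 0.125. The stated arm sizes therefore suggest some restriction that the article does not describe.

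**5. What an uneven split would do.** Assume that sex shifts an outcome by 0.3 SD; this figure is not in the documents. The shift in the arm difference is the difference in the proportion of men × 0.3.

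- 12/8: (12 − 8)/20 × 0.3 = 0.06 SD
- 13/7: (13 − 7)/20 × 0.3 = 0.09 SD
- 14/6: (14 − 6)/20 × 0.3 = 0.12 SD

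The shift scales in proportion to the assumed sex effect. For comparison, the standard error of a difference between two arms of 20 is √(2/20) = 0.32 SD.

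**The case against.** The strongest reply is that nothing here is stated outright. The order is inferred, listing baseline tests under each arm is an ordinary way of describing what each arm undergoes, and the flow diagram and schedule may show the order. This stands as a limit on the wording, but it does not dispose of the point: the text that is shown leads a site to allocate first, and no sentence leads it the other way.

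A reader might infer more than the documents support.

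- *The list is unstratified.* The article is silent. A condensed article may leave list construction to the full protocol, and 10 men and 10 women per arm is compatible with Section 2.2. The probabilities above are conditional on no stratification.
- *All baselines are compromised.* The study hypothesis concerns HbA1c and glucose. These are read by device, do not depend on effort, and are taken by someone other than the platform operators.
- *Sex imbalance biases the trial.* Chance imbalance does not bias a randomised comparison in expectation. Comparing changes removes much of any stable difference in level, and Section 2.7 already allows regression adjustment.
- *Controls will leave on learning their arm.* Section 2.8 lets participants leave when they wish, but the Discussion expects drop-out only for strong reasons. The loss is possible and cannot be sized.

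Two further limits apply. Section 2.7 does not list the functional tests among its bivariate variables, although Section 2.6 says they are measured for before-and-after comparison. Also, the platform operators would still run these tests at 12 weeks, so changing the order of randomisation does not cure that part of the blinding problem.

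**Conclusion.** The point holds in a limited form. As the protocol reads, allocation appears to precede baseline. If it is carried out that way, the baseline TUG, 10MWT and 5STS could be influenced by knowledge of the arm, and anyone leaving in the interval would contribute nothing. The size of the distortion cannot be derived from the documents. It would pass in full into a comparison of changes, and HbA1c and lipids are much less affected. The conclusion rests on reading Sections 2.5, 2.5.1, 2.5.2 and 2.6 together, and on participants being told their arm when they are allocated. It is worth correcting because the change is nearly free beforehand and impossible once baselines have been taken.

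The sex issue is secondary. If the list is not stratified, a split of 12/8 or worse has probability 0.34. Under the assumed 0.3 SD sex effect, splits of 12/8 to 14/6 shift the difference by 0.06 to 0.12 SD. Stratifying would be a modest gain in precision, not the removal of a bias.

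**What to change.** **Main change (Sections 2.5 and 2.6).** State that randomisation takes place only after all baseline measurements are recorded, at the end of the second week of February, and that participants learn their arm and session timetable then. Sections 2.5.1 and 2.5.2 should describe baseline as common to all participants before allocation.

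*Cost:* the timetable, which both sections now give out at the information stage, goes out about a week later, so participants have shorter notice before the first session. The 12-week intervention period need not move.

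**Secondary change (Sections 2.2, 2.5 and 2.7).** Generate the list in balanced blocks within sex, giving 10 men and 10 women per arm, and include sex in the planned linear regression. If the full protocol already stratifies, the article need only say so.

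*Cost:* one list to generate and one term in the model. If the sponsor also wants the list held by someone who neither recruits nor measures, an additional person may be needed, since all three researchers described in Section 2.5 take measurements.

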#### 2.5.1. Control Group

Participants in the control group will undergo a determination of glycosylated hemoglobin, blood pressure, lipid profile, weight and height, as well as functional tests such as TUG, 10MWT, and 5STS. Subsequently, they will be encouraged to continue their normal life, insisting on the importance of glycemic controls before and after their daily physical exercise, in addition to continuing with the dietary measures recommended by their specialist. After 12 weeks, glycosylated hemoglobin, blood pressure, lipid profile, weight, height, and the TUG, 10MMT, and 5STS tests will be redetermined.

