## 2. Materials and Methods

The hypothesis of this study will be that the use of whole-body vibration has an effect on type 2 diabetes mellitus by decreasing the levels of glycosylated hemoglobin and blood glucose.

The objective of the study will be to analyze the decrease in glycosylated hemoglobin and blood glucose levels after the use of whole-body vibration platforms at baseline and at 12 weeks in people diagnosed with type 2 diabetes mellitus.

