#### 2.5.2. Experimental Group

Participants in the intervention group will be subjected to the following tests:-At the beginning of the intervention, a determination of glycosylated hemoglobin, blood pressure, lipid profile, weight, height, and TUG, 10MWT, and 5STS, which will be repeated after 12 weeks of intervention.-Before each training session, participants will undergo a basal blood glucose and blood pressure measurement, which will be repeated after the end of the session.-Each training session on the vibrating platform is composed of 6 exercises, with a duration of 60 s, with 60 s pauses between exercises and a warm-up exercise:

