**Warm-up exercise: classic squat**

Prior to the training session, the subjects will place their feet on the floor at shoulder height, with their arms stretched forward to gain stability; the knee will be reflected at 100° and the back will be kept straight, returning to the starting position.

1.Alternating feet exercise.

With the back to the platform and the feet completely straight, the subjects will bend the knee while keeping the other leg straight. Then, they will alternate and do the same with the other leg for the duration of the exercise.

2.Up and down exercise.

Starting from the standing position on the platform, subjects will lower the right–left foot and then raise the right–left foot, repeating the exercise for 60 s.

3.Stride exercise

The subjects, starting from the initial standing position, will be separated at shoulder width and then place one foot on the platform, bending the knee at 90°, and the other on the floor. The exercise will be carried out with both legs alternately, holding the handlebars of the platform to maintain balance.

4.Heel Raise Exercise

The subjects, starting from the initial standing position, will be separated at shoulder width and raise their heels, keeping their knees slightly bent, their back straight, their eyes straight ahead, and holding the handlebars of the platform to maintain their balance.

5.Squat exercise

Starting from a standing position, shoulder-width apart, the subject will perform a 100° knee flexion, returning to the starting position.

6.Squat exercise with weight changes.

Starting from the squat position, the subject will perform a knee flexion–extension while shifting body weight in the mid-lateral axis (left–right) alternately.

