## 3. Discussion

Aerobic physical exercise of moderate intensity is recognized as an effective nonpharmacological approach to reduce glycemia. The physiological modifications observed with WBV are analogous to those of any physical activity and, in addition to acute changes, chronic adaptations in the mechanical behavior of the muscles have been described. It is known that muscles react to vibration by contracting and stretching automatically. Vibration triggers a muscle contraction reflex, the TVR, which causes an increase in hormone secretion, among others [18]. That is why WBV could be a type of physical exercise to reduce glycemia and HbA1c, in addition to lipid profile, weight, height, functional balance, and neuropathic pain [12,19,20,21,22]. However, studies such as that of Behboudi et al. [23], after 12 weeks of whole-body vibration intervention, did not show a significant reduction in HbA1c. Another study by Liphardt et al. points in the same direction that bone quality in osteopenic postmenopausal women is not improved after 12 months of whole-body vibration training [24].

It is important to differentiate between vibratory devices that subject the body to vibration while the body is kept relaxed or resting on couches or beds (oscillatory-cyclic and oscillatory-cycloid vibration [3,12]) and WVB devices where the patient performs a voluntary exercise while adding the vibratory stimulus, affecting the whole body placed on top of a vibrating platform. It is a voluntary and conscious exercise to which the vibratory stimulus is added.

Since it is a physical exercise different from that practiced by the general population, it is new, and the sessions are of short duration, it could be estimated that the abandonment of the sample will only occur due to a very justified cause, which will reduce the negative results of the research.

HbA1C is one of the most determinant parameters in the diagnosis and long-term control of DM. According to the ADA [4], an HbA1c > 6.5% is considered a diagnostic criterion for DM, while values < 7.0% HbA1c determine good blood glucose control in the last four months.

This fact would behave as a protective factor in the development of certain cardiovascular diseases in people with DM 2, since it has been shown that the reduction in HbA1c in blood reduces the risk of developing heart disease by around 14% and, in addition, the risk of mortality [25,26].

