## 4. Conclusions

The whole-body vibration intervention for type 2 diabetics will allow testing of its influence on glycosylated hemoglobin and capillary glycemia levels, lipid levels after the intervention, as well as on blood pressure, body mass index, and functional balance. In addition, the aim is to test the effectiveness of the whole-body vibration platform as a method of physical exercise, improving patient adherence and its use in health centers.

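### The hypothesis credits vibration, but the comparison with usual life can only test the whole supervised exercise-on-platform programme

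*Protocol article*

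**What the plan says.** **Hypothesis and mechanism.** Section 2 (Materials and Methods) gives the hypothesis: "the use of whole-body vibration has an effect on type 2 diabetes mellitus by decreasing the levels of glycosylated hemoglobin". It names glucose as a second outcome. In the same section, the stated objective refers to use of the platforms and names no comparator. The Introduction describes whole-body vibration as vibration that enters the body of a person standing on a platform, and bases its effects on the tonic vibration reflex. The Discussion repeats that mechanism.

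**Experimental arm.** Section 2.5.2: "Each training session on the vibrating platform is composed of 6 exercises, with a duration of 60 s, with 60 s pauses between exercises", plus a warm-up. The exercises are active in themselves. For the squat, for example: "Starting from a standing position, shoulder-width apart, the subject will perform a 100° knee flexion, returning to the starting position". Section 2.5 makes two researchers responsible for the platform settings and "for the correct performance of the exercises proposed for each training session". Glucose and blood pressure are measured before and after every session. Section 2.6 sets three sessions a week for 12 weeks.

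**Control arm.** Section 2.5.1: "they will be encouraged to continue their normal life". Controls are also urged to check glucose around their own exercise and to keep to their dietary advice. No exercise programme, inactive platform or matched contact is assigned.

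**How the article describes its own intervention.** Discussion: "It is a voluntary and conscious exercise to which the vibratory stimulus is added". Section 4 says that the intervention "will allow testing of its influence on glycosylated hemoglobin and capillary glycemia levels", and then describes the platform as a way of taking physical exercise.

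**The concern.** The hypothesis names vibration as the cause, but the arms differ in several things at once. A lower HbA1c in the experimental arm could come from the vibration, the exercises, the supervision and contact, the staff-run monitoring, or any mixture of these. If the hypothesis stands as worded, a positive result is likely to be reported as a vibration effect.

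The distinction has practical weight. The Introduction presents vibration therapy as attractive for people who cannot or fear to exercise. That use depends on vibration contributing something apart from exercise. Yet this trial delivers vibration only through active exercise, and section 2.2 excludes people whose comorbidities are incompatible with exercise.

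**Working it through.** **1. Session length, as a check on the schedule.** Six exercises of 60 s, each followed by 60 s of rest, give 6 × (60 + 60) s = 720 s = 12 min. This matches the 12 min in the Abstract. Pauses only between exercises would give 6 × 60 + 5 × 60 = 660 s = 11 min. The active time is the same either way.

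**2. Size of the non-vibration difference between arms.**
- Sessions: 3 per week × 12 weeks = 36.
- Active exercise per session: 6 × 60 s = 6 min.
- Active exercise per week: 3 × 6 = 18 min.
- Active exercise in total: 36 × 6 = 216 min, not counting the warm-up, whose length is not given.
- Staff measurements of glucose and of blood pressure around sessions: 36 × 2 = 72 occasions.

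The control arm is assigned none of these. Controls keep their own daily exercise and are urged to check glucose around it, so glucose monitoring is not absent there, but it is not done by staff at sessions.

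**3. Components by arm.**

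| Component | Experimental | Control |
|---|---|---|
| Vibration (14 Hz, 2 mm) | yes | no |
| Assigned exercise programme | yes | no |
| Supervision and session contact | yes | no |
| Staff monitoring at each session | yes | no |
| Own usual lifestyle | yes | yes |

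**4. What the contrast estimates.** Let V, E, S and M be the effects of vibration, exercise, supervision with contact, and session monitoring, with any interactions I. Relative to usual life:

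expected difference (experimental − control) = V + E + S + M + I.

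This is one equation with several unknowns. The same difference arises whether V is all of it or none of it. A larger sample narrows the interval around the sum and does nothing to divide it.

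**5. Whether the planned analysis can divide it.** Section 2.7 plans between-group comparisons and linear regression for confounding factors. In the first four rows of the table every component is present in all of one arm and absent in all of the other. An indicator for assigned exercise would therefore be the same variable as the arm indicator. Regression cannot separate them.

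**6. Whether the limit is disclosed.** The Study Limitations name footwear, diet and the season's influence on HbA1c. They do not mention that vibration is inseparable from exercise, supervision and contact.

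**The case against.** The strongest reply is that the article defines its intervention as the package. The Discussion sets passive vibration devices apart from platforms on which the person exercises, and the sentence "It is a voluntary and conscious exercise to which the vibratory stimulus is added" belongs to that definition. The Introduction calls the approach a physical activity treatment. In section 4 the thing whose influence is to be tested is the intervention, and the next sentence treats the platform as a form of exercise. On that reading, usual life is a legitimate comparator for an add-on programme, and the randomised difference answers the question asked.

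Much of this stands, and it rules out three stronger readings.

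- *That the design is invalid or needs a sham or exercise-only arm.* The documents do not support this. The package effect is a proper estimand, and separating the components is not a stated aim of this 40-person pilot.
- *That the conclusion claims a vibration-specific effect.* The words "will allow testing of its influence on glycosylated hemoglobin and capillary glycemia levels" could be read so in isolation, but their subject is the intervention.
- *That the article concedes these exercises alone would lower HbA1c.* The Discussion credits lower glycaemia to moderate aerobic exercise. It does not say that 18 minutes a week of squats, strides and heel raises would do it.

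What the reply does not remove is the inconsistency. The Introduction defines whole-body vibration by the vibration and explains its effects by a reflex to vibration, and the hypothesis uses that term without the package definition that comes only in the Discussion. The two readings support different conclusions, and the limitations are silent.

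**Conclusion.** The point holds as a mismatch between the stated hypothesis and the comparator. It is not a fatal design flaw. The trial can estimate the effect of a supervised exercise programme on a vibration platform against usual lifestyle. It cannot attribute any part of that effect to vibration, and the article does not say so.

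The non-vibration difference between the arms is 36 supervised sessions and 216 minutes of active exercise per participant at full attendance. The vibration share of any effect is unidentified. That is a property of the two-arm contrast, not an estimate that the share is small.

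This rests on two things: the arms being delivered as sections 2.5.1, 2.5.2 and 2.6 describe, and no exercise or contact being assigned to controls beyond what is written. It does not assume that the exercises alone work, only that the design cannot show that their contribution is nil.

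**What to change.** 1. In section 2, and in the matching wording of the Abstract, restate the hypothesis and objective as the effect on HbA1c and blood glucose of a 12-week supervised exercise programme on a vibration platform, compared with usual lifestyle.
2. In section 4, keep the conclusion explicitly to the programme.
3. In the Study Limitations, add that the design does not separate vibration from exercise, supervision and contact, so any effect belongs to the programme as a whole. The tonic vibration reflex can stay as background, marked as a mechanism that the trial does not test.

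No arm, participant, measurement or analysis changes. The cost is wording and a less specific claim: a positive result would support the programme and would leave the contribution of vibration open for a trial with a different comparator.

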## Abstract

Diabetes generates a great impact on society, as well as a concern for health professionals due to its high and increasing prevalence; there are several studies that demonstrate the effectiveness of vibration platforms and their benefits at a physiological level. The aim of this study will be to analyze the decrease in glycosylated hemoglobin and glycemia levels after the use of whole-body vibration platforms and the possible inclusion of this therapeutic option within the usual treatments. This is a double-blind, randomized controlled trial with parallel group design in a 1:1 ratio. The sample will be composed of people diagnosed with type 2 diabetes mellitus in in the Plasencia area (Cáceres, Extremadura). Participants will be randomly assigned to the intervention or control group using a randomization list and will follow the inclusion criteria: type 2 diabetics between 50 and 60 years of age and not taking diabetes medication. All participants will undergo a determination of glycosylated hemoglobin, blood pressure, lipid profile, weight and height, and different functional tests such as Time Up and Go, 10 Meters Walk Test, and 5 Sit To Stand. The experimental group will perform a whole-body vibration intervention on an oscillating platform for 12 weeks with a weekly frequency of three nonconsecutive days and a duration of 12 min. The exercises will consist of 60 s of work and 60 s with rest. The control group will carry out their normal life insisting on the importance of glycemic controls before and after their daily physical exercise. This study has been registered at clinical.trial.org, ID: NCT 05968222. Whole-body vibration platforms have demonstrated their effectiveness in different pathologies such as stroke, fibromyalgia, sclerosis multiple, or Parkinson’s. For that reason, an improvement in glycemic and lipid values and body composition are expected in people with diabetes after a whole-body vibration intervention for 12 weeks’ duration. In addition, whole-body vibration platforms could be postulated as an alternative to usual treatments.

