### Study Limitations

Among the possible limitations contemplated in the present study are the diversity of the different footwear of each patient, the nutritional habits of the participants due to not being able to follow an exhaustive control of the diet consumed, and the influence of climate on HbA1c. According to the study by Tseng et al. [36], it will be concluded that HbA1c has higher values depending on the season of the year; thus, during the winter, the values are higher than during warmer seasons. Our work will be performed during the winter and spring, so the different results may be influenced by these seasons.

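### As described, self-care advice goes to the control group and supervised glucose readings to the experimental group, so the arms differ in more than vibration training

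*Protocol article*

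**What the plan says.** **All participants.** Section 2.5 (Procedure) gives one general instruction: "Patients will continue with their usual lifestyle". It mentions neither diet nor glucose checks.

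**Control group.** Section 2.5.1 lists baseline tests and the same tests at 12 weeks. Between them, controls are encouraged to carry on with normal life, with staff "insisting on the importance of glycemic controls before and after their daily physical exercise". A reminder about diet is attached: "in addition to continuing with the dietary measures recommended by their specialist". The abstract describes the control condition in similar terms: "The control group will carry out their normal life insisting on the importance of glycemic controls before and after their daily physical exercise". It does not mention diet.

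**Experimental group.** Section 2.5.2 lists the baseline and 12-week tests, the readings around sessions and the exercises. On the readings it says: "Before each training session, participants will undergo a basal blood glucose and blood pressure measurement". These are repeated when the session ends. Section 2.6 sets three sessions a week for 12 weeks. Neither section mentions dietary or self-monitoring advice.

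**Diet in general.** Study Limitations names "the nutritional habits of the participants due to not being able to follow an exhaustive control of the diet consumed" as a possible limitation, without separating the arms.

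**The concern.** The study objective is the change in HbA1c and blood glucose. Advice to check glucose around exercise can change behaviour that bears on those outcomes. If staff give it to one arm after allocation, it is a co-intervention that randomisation does not balance. The experimental arm has an unmatched element of its own, namely regular glucose readings in the presence of staff.

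What is at stake is attribution. A difference between groups at 12 weeks would be the combined result of vibration training, control-only advice, and session readings with staff contact. The linear regression in section 2.7 cannot separate these, because an element given to a whole arm and withheld from the other coincides with allocation. The remedy therefore lies in how the arms are specified, not in the analysis.

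**Working it through.** The protocol gives no figure on this point, so there is none to reproduce. The check sets the descriptions of the two arms side by side.

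| Element | Control group | Experimental group |
|---|---|---|
| Keep usual lifestyle | Yes (2.5, all patients) | Yes (2.5, all patients) |
| Insistence on glucose checks around daily exercise | Yes (abstract; 2.5.1) | Not mentioned (abstract; 2.5.2; 2.6) |
| Reminder to continue existing dietary measures | Yes (2.5.1 only) | Not mentioned (2.5.2; 2.6) |
| Glucose readings around training sessions | None described | Before and after every session (2.5.2) |
| Vibration training | No | Yes (2.5.2; 2.6) |

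**Amount of monitoring in the experimental arm.** Inputs: 12 weeks and 3 sessions a week (abstract; 2.6), with one glucose reading before and one after each session (2.5.2).

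- Sessions: 12 × 3 = 36.
- Readings per participant with full attendance: 36 × 2 = 72.

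**How firm each difference is.**

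1. *Glucose-check advice.* It is stated twice, each time as part of the control condition, and the wording is insistent. The usual-lifestyle line does not naturally cover it. This is the firm part.
2. *Dietary reminder.* It is stated once and asks controls to continue measures that their specialist has already recommended. For the experimental group, the same may be implied by keeping the usual lifestyle. This part is weak.
3. *Session readings.* They are clearly confined to the experimental arm. They are measurements, not self-care advice, but they are repeated glucose information obtained in contact with staff.

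**Direction.** If advice to controls improves their glycaemia, it shrinks an apparent benefit of vibration. If session readings and staff contact improve glycaemia in the experimental arm, they enlarge it. The documents give no size for either, so the sign of the net effect is open.

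**Size.** A calculation would need the effect of the advice on HbA1c, the effect of the session readings and contact, and the standard deviation of HbA1c. The documents give none of these, so no figure is offered.

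**The case against.** The strongest reply is that the experimental side rests on silence. Nothing says that the experimental group is denied the advice. Section 2.5.2 presents itself as a list of tests and exercises, not of counselling, and a journal article condenses a fuller protocol that may give the same advice to both arms. The abstract is shorter still, so its silence about the experimental arm adds little. This stands as a limit on certainty, but it does not remove the point. The advice is stated positively and tied to one arm in two places, and advice meant for everyone would sit beside the usual-lifestyle line in 2.5. A team following the text as written would give it to controls only.

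A second reply is that glucose checking is partly matched, since the experimental group is measured around every session. That is fair: the arms differ in the form of glucose checking, and neither goes without it. The forms are not equivalent, however. One is advice about daily life and the other is measurement at supervised sessions.

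Three stronger readings are tempting, and the documents do not support them:

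- *A new dietary intervention in controls.* A reader might infer this from 2.5.1, but the text only has controls continue existing measures, and the abstract leaves diet out.
- *A known bias towards no effect.* This counts the advice to controls and ignores 36 sessions of readings and contact in the other arm.
- *An admission that diet is unbalanced.* Study Limitations says that diet cannot be closely controlled among participants in general. It describes no imbalance between arms.

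**Conclusion.** The point holds in a limited form. As described, the arms differ in self-care advice and in glucose monitoring as well as in vibration training, and both can bear on the outcomes named in the objective. This makes a difference in HbA1c or glucose harder to attribute to vibration.

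The size and net direction of any bias cannot be determined. A reader might express it as a share of the difference that the trial could detect. That would need an assumed effect of the advice, an assumed standard deviation, and an alpha and power that the protocol does not state. Section 2.2 also describes the 40 participants as a pilot to obtain data for a sample size calculation, so detectable difference is a doubtful yardstick.

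The conclusion assumes that the text is followed as written and that no fuller document already gives both arms the same advice. If one does, a single clarifying sentence settles the matter. The conclusion does not depend on the sample size or on any assumed effect. It is a change worth making because it is nearly free, and it does not by itself invalidate the trial.

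**What to change.** Reconcile the abstract and sections 2.5, 2.5.1 and 2.5.2:

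- Move whatever self-care advice is given out of 2.5.1 and into 2.5, as an instruction to all participants.
- State that it is delivered identically to both groups, in the same written form and at the same visit.
- State in 2.5.2 that the glucose readings around sessions are the only planned difference in monitoring between the arms.
- Edit the abstract so that the advice no longer appears as a feature of the control condition alone.

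The clinical content of the advice is for the investigators. The request is only that both arms receive the same. The cost is one shared information sheet and a few edited sentences. The session readings remain an unmatched element, but a declared one that can be taken into account when the result is read.
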